## Abstract

**Background:**

A large proportion of people who inject drugs (PWID) living with hepatitis C virus (HCV) infection have not been treated. It is unknown whether inclusion of HCV diagnostics and treatment into integrated substance use disorder treatment and care clinics will improve uptake and outcome of HCV treatment in PWID. The aim is to assess the efficacy of integrating HCV treatment to PWID and this paper will present the protocol for an ongoing trial.

**Methods:**

INTRO-HCV is a multicentre, randomised controlled clinical trial that will compare the efficacy of integrated treatment of HCV in PWID with the current standard treatment. Integrated treatment includes testing for HCV, assessing liver fibrosis with transient elastography, counselling, treatment delivery, follow-up and evaluation provided by integrated substance use disorder treatment and care clinics. Most of these clinics for PWID provide opioid agonist therapy while some clinics provide low-threshold care without opioid agonist therapy. Standard care involves referral to further diagnostics, treatment and treatment follow-up given in a hospital outpatient clinic with equivalent medications. The differences between the delivery platforms in the two trial arms involve use of a drop-in approach rather than specific appointment times, no need for additional travelling, less blood samples taken during treatment, and treatment given from already known clinicians. The trial will recruit approximately 200 HCV infected individuals in Bergen and Stavanger, Norway. The primary outcomes are time to treatment initiation and sustained virologic response, defined as undetectable HCV RNA 12 weeks after end of treatment. Secondary outcomes are cost-effectiveness, treatment adherence, changes in quality of life, fatigue and psychological well-being, changes in drug use, infection related risk behaviour, and risk of reinfection. The target group is PWID with HCV diagnosed receiving treatment and care within clinics for PWID.

**Discussion:**

This study will inform on the effects of an integrated treatment program for HCV in clinics for PWID compared to standard care aiming to increase access to treatment and improving treatment adherence. If the integrated treatment model is found to be safe and efficacious, it can be considered for further scale-up.

**Trial registration:**

ClinicalTrials.gov.no. NCT03155906.

## Background

Hepatitis C virus (HCV) is endemic among people who inject drugs (PWID) [1]. Globally 40% of the HCV disease burden is attributable to injecting drug use and in Western Europe this fraction is 64%. Recently, highly effective direct-acting antiviral (DAA) treatment of HCV infection became available, prompting the World Health Organisation (WHO) to develop a global strategy to eliminate HCV by 2030. However, as PWID represent the majority of HCV patients in high income countries there are challenges particular to this group that must be addressed if elimination is to be achieved [2].

Chronic HCV infection is a slowly progressive disease that may lead to liver cirrhosis and subsequent complications, including hepatocellular carcinoma (HCC), liver failure and early deaths [3, 4]. Among HCV-infected people with opioid dependence, one-third develops advanced liver disease within three decades [5] and within this group, liver disease and drug overdose becomes equally common causes of death among individuals over the age of 50 years [6]. Reports from opioid agonist therapy (OAT) clinics in Norway indicate that more than half of patients receiving OAT have chronic HCV infection [7]. This represents an ageing cohort often at high risk of developing advanced liver disease [8]. Ongoing injecting risk behaviour with risk of onwards HCV transmission is also prevalent in this population [9]. Thus, reaching these individuals with HCV treatment is of critical importance both to reduce HCV disease burden and HCV transmission.

Until 2014, HCV treatment was interferon-based with low efficacy, considerable adverse effects and accordingly low treatment uptake particularly among PWID [10]. The perceived high risk of reinfection following successful treatment may also have represented a barrier to HCV treatment in this population [9]. The current availability of tolerable and highly efficient all-oral DAA treatment has changed the HCV care paradigm and led to significant therapeutic optimism. However, The World Hepatitis Summit in 2017 expressed concern for the lack of integrated approaches, acknowledging the need for new models of patient-centred service delivery and recognised the need for integrated collaborative approaches [11]. To achieve this, new models of care must be developed. Models focusing on interdisciplinarity, availability and accessibility, with decentralised clinics and frequent follow-ups have been suggested to be effective [12–14]. However, reviews have called for further evidence on the effect of integrated treatment for people with substance use disorders [15, 16].

In Western Norway, more specifically in the cities of Stavanger and Bergen, OAT treatment is administered in an integrated treatment and care model with follow-up by physicians, nurses, social workers and psychologists on nearly a daily basis with observed intake of OAT medications [17]. PWID not receiving OAT are offered care at municipal low-threshold health and care clinics. Thus, the models already in place could be a well-suited platform to evaluate the effect of integrated HCV care to PWID.

### Objectives

This paper presents the protocol of the INTRO-HCV study. The primary objective of the INTRO-HCV study is to compare the efficacy of integrated treatment of HCV in PWID with the current standard treatment. Integrated treatment includes testing for HCV, assessing liver fibrosis with transient elastography, counselling, treatment delivery, follow-up and evaluation provided by integrated substance use disorder treatment and care clinics. Most of these clinics for PWID provide OAT while some clinics provide low-threshold care without OAT. Standard care involves referral to further diagnostics, treatment and treatment follow-up given in a hospital outpatient clinic with equivalent medications.

Secondary objectives are comparison of treatment adherence between the integrated and standard arms, assessment of changes in quality of life, fatigue and psychological well-being before and after HCV treatment, as well as changes in drug use, infection related risk behaviour, and risk of reinfection among those with sustained virologic response (SVR). Further, we will estimate cost-effectiveness of integrated HCV care and incidence and prevalence of HCV infection among PWID in Bergen and Stavanger to assess population effects of scaling up treatment.

## Methods

### Study design

This is a multicentre, randomised controlled clinical trial.

### Study settings and participants

The target group will be PWID receiving integrated substance use disorder treatment and care from involved clinics in Bergen and Stavanger who are chronically infected with HCV and eligible for treatment according to national guidelines.

Department of Addiction Medicine at Haukeland University Hospital in Bergen have adopted an integrated treatment and care model for PWID receiving OAT. In Bergen, OAT outpatient clinics have been established in each district where the patients are followed up by health and social workers on a nearly daily basis with observed intake of the OAT medications such as buprenorphine or methadone [17]. Every month, the OAT clinics have a total of 6000 visits among the approximately 500 patients. This group of patients have a large morbidity burden and have to a limited extent been able to get access to other standard health care. Each of the OAT outpatient clinics is staffed by a consultant and a physician/ specialist registrar in addiction medicine in addition to nurses, social workers, and psychologists. A close collaboration has been established between the Department of Addiction Medicine and the Agency for addiction and mental health in Bergen municipality, who is responsible for the care in several of the primary health clinics for PWID in Bergen. Clinics for PWID in the Stavanger area have a relatively similar structure and are responsible for the OAT treatment of approximately 460 patients within their area. People receiving OAT in Norway are generally prescribed buprenorphine or methadone, to some degree additional benzodiazepines but rarely other opioids. The treatment model in Bergen and Stavanger is a well-suited platform to test integration of HCV treatment aiming to improve the health and life span of a vulnerable group, and at the same time gathering knowledge which traditionally have been difficult to obtain.

### Eligibility criteria

For the randomised trial, inclusion will be based on the following criteria
PWID receiving OAT or low-threshold care from an included clinic with follow-up on weekly basisChronically infected with HCV (HCV RNA positive measured at least twice over 6 months)Eligible for treatment according to national guidelines (criteria specified below)Giving informed consent

Enrolment started May 2017. At that time, eligibility for treatment according to Norwegian guidelines was defined as follows:
Genotype 1 and 4 infection independent of stage of liver fibrosis.Genotype 2 and 3 infection with significant liver fibrosis.

Transient elastography (FibroScan) will be used in the screening of significant fibrosis defined as measurements above 7.0 kPa [18, 19].

Thus, some patients needed to wait some months after HCV diagnosis before initiating treatment. From 1st of February 2018, all patients with chronic HCV were eligible for treatment according to the updated national (independent of stage of liver fibrosis).

The following exclusion criteria will be used:
HIV co-infectionSevere extrahepatic HCV manifestations (e.g. cryoglobulinemia)Membranoprolifereative glomerulonephritis (MPGN) or renal failure (estimated glomerular filtration rate < 30 ml/min/1.73 m^2^)Decompensated liver disease (Child-Pugh score > 6 points, class B and C)

Encephalopathy in Child-Pugh will be assessed according to the West Haven criteria [20].
Currently receiving treatment for HCV

### Interventions

Participants randomised to standard care are first assessed and diagnosed at the integrated care clinics for PWID by nurse and physician and when found in need of treatment, are referred to a hospital clinic for further assessment and treatment. The standard care generally involves being referred to the medical outpatient clinic. The clinic will send a letter informing on time of appointment usually some weeks later and could involve some additional blood samples and imaging before initiating DAA treatment. Subsequently, an electronic prescription is given in a consultation where treatment is initiated. The medications given are in principle equivalent in the two trial arms. Most will receive medication combinations of either elbasvir/grazoprevir 50/100 mg or sofosbuvir/ledipasvir 400/90 mg (for genotype 1 and 4) or sofosbuvir/velpatasvir 400/100 mg (for genotype 2 and 3) – sometimes also in combination with voxilaprevir 100 mg or ribavirin 200 mg due to specific clinical indications. Glecaprevir/pibrentasvir 100/40 mg may also be used in special cases. Patients are generally given follow-up consultations every 4 weeks during treatment and a post-treatment assessment 12 weeks after completed treatment. Typically, this involves a total of 4–5 consultation visits at the hospital.

Participants randomised to integrated treatment are given integrated assessment and treatment at the clinics for PWID (by nurse and physician). For those found to be in need of treatment, medications are made available by a nurse that gives follow-up for OAT or low-threshold care for PWID. Follow-up during treatment is given in parallel with delivery of OAT treatment and other care. At 12 weeks post treatment, a research nurse takes blood samples to assess the treatment effect.

The differences between the delivery platforms in the two trial arms involve the following main aspects:
Need of travel: Standard care involves transportation to a hospital clinic – a distance that ranges from 1 to about 25 km in distance (with potential travel costs) while integrated treatment does generally not require need for additional travelNeed to come to specific appointment times: Standard treatment is generally given based on appointments while integrated treatment is generally given in a drop-in approachFrequency of blood samples during treatment is mainly depending on clinical indication (e.g. suspected adverse effects or complications). Less blood sampling may reduce discomfortTime used and potential for overlapping appointments: For standard treatment there is a higher risk that the appointment time overlap with other important activity including other health care, while for integrated treatment appointment time is generally planned together with patientNeed to meet new clinicians for health care: In integrated care clinics, follow-up is generally done by already familiar contact nurse and physician providing regular follow-up. Standard treatment is given in hospital clinic by clinicians often unfamiliar to the patients

### Outcomes

Primary outcome measures are
Sustained virologic response will be assessed by undetectable HCV RNA at 12 (range 10–14) weeks after completed treatment. The virologic blood samples in Bergen will be analysed at Department for microbiology (accredited by ISO-standard 15,189) after being centrifuged at each study clinic before transferTime to treatment initiation after diagnosing HCV in need of treatment (in line with national guidelines). This will be assessed with time-to-event analyses. We also plan to present stratified analyses on patient-related delay and system-related delay

Secondary outcome measures are
Treatment adherence assessed by proportion of doses observed being taken in intervention group and reported obtainment from pharmacies of the prescribed drugs combined with self-reported questions on adherence collected at 4, 8 (and 12 for treatment recommended beyond 8 weeks) weeks after treatment initiation. The self-reported questions categorise adherence during last four weeks into rarely, sometimes but less than half of the doses, between 50 and 80% of the doses, more than 80% of the doses, and always (95% of doses or more). These outcome measures will be collected at the OAT/PWID clinicsReinfection will be defined as HCV RNA recurrence following SVR. Incidence rates will be calculated using person-time techniques assuming a Poisson distribution. All patients achieving SVR will be assessed for reinfection 3 months after treatment and then annually. HCV RNA positive samples will be further analysed with a quantitative HCV RNA count, HCV genotyping. Relapse is defined as presence of the same virus strain at the time of diagnosis and at the end of treatment. Anti-HIV and use of other drugs will also be assessedChanges in quality of life will be assessed with the questionnaire EQ-5D-5 L (https://euroqol.org/eq-5d-instruments/) in addition to a self-reported question on happiness on a 0 to 10 scale at 12 weeks after treatment compared to before treatmentChanges in fatigue will be assessed with the Fatigue Symptom Scale at 12 weeks after treatment compared to before treatmentChanges in psychological well-being will be assessed with the Norwegian validated translation version of Hopkins Symptom Checklist (SCL-10) at 12 weeks after treatment compared to before treatmentAssessment of changes in substance use will be assessed with self-reported use of the following drug categories the last 30 days, the last 12 months and ever: Alcohol, tobacco, cannabis, amphetamines, cocaine, heroin, other opioids not prescribed by physician, benzodiazepines or z-hypnotics, hallucinogens, solvents and gamma hydroxybutyrate (GHB), anabolic steroids and other drugs at 12 weeks after treatment compared to before treatmentAssessment of changes in injecting risk behaviour will be performed with questions assessing sharing of needles and other user equipment before and after HCV treatment at 12 weeks after treatment compared to before treatmentHealth provider costs by using an ingredients approach, where quantities used and the value (or price) of each unit is estimated in the both trial arms. Health care costs will be used in a health economic evaluation, where both costs per cured patient and per Quality Adjusted Life Year (QALY) gained will be estimated.

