### Recruitment

All PWID receiving OAT treatment or low-threshold care from included clinics will be considered the reference target population. As part of an annual clinical assessment, patients will be informed about the study and asked for consent to participation. All patients in target population will be offered annual clinical assessment and study participation. For those giving informed consent, an extended clinical assessment will be offered and those diagnosed with chronic HCV will be randomised for the intervention.

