### Analyses and statistical methods

A detailed plan for analysis will be developed before data export and analysis. We will in this section outline some of the principles which will be used to guide decisions during data analysis. Analysis methods will follow the CONSORT and SPIRIT guidelines as far as possible [22–24]. All tests will be two-sided. Descriptive results and efficacy estimates will be presented with 95% confidence intervals. The statistical significance is set at *p* < 0.05. Potential confounders may be considered for adjustment if they are imbalanced at baseline (with assumed meaningful differences). Missing data will be considered, and appropriate imputations based on pre-defined assumptions will be done when necessary (as described in detailed plan of analysis). Categorical variables will be summarized as percentages and continuous variables as medians with interquartile ranges or means with standard deviation for variables with a Gaussian distribution. The main outcomes will be analysed with time-to-event analysis (Cox regression and Kaplan-Meier plots) and generalised linear models/logistic regression. A separate health economic evaluation will assess the incremental cost-effectiveness ratio of the intervention arm compared to the control arm. A Markov model will be used, and the analysis will be exhibited in TreeAge. Results will be presented as cost per QALYs of integrated versus standard HCV care.

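### The primary time-to-initiation clock starts at a finding of treatment need, not at randomisation, and the protocol is inconsistent on whether that point comes before or after allocation

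*Protocol article*

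**What the plan says.** All references are to the protocol article.

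- **Outcomes.** The second primary outcome is time to "treatment initiation after diagnosing HCV in need of treatment (in line with national guidelines"), assessed by time-to-event methods. Analyses separating patient-related from system-related delay are also planned.
- **Analyses and statistical methods.** "The main outcomes will be analysed with time-to-event analysis (Cox regression and Kaplan-Meier plots) and generalised linear models/logistic regression". No time origin is given here.
- **Eligibility criteria.** One inclusion criterion for the randomised trial is "Eligible for treatment according to national guidelines (criteria specified below"). The section adds that, under the guideline in force when enrolment began in May 2017, "some patients needed to wait some months after HCV diagnosis before initiating treatment". From 1 February 2018 all chronic HCV was eligible.
- **Recruitment.** After consent and an extended assessment, "those diagnosed with chronic HCV will be randomised for the intervention".
- **Interventions.** The account of the standard arm opens: "Participants randomised to standard care are first assessed and diagnosed at the integrated care clinics for PWID by nurse and physician". Referral depends on a later finding of need by the same staff. For the integrated arm: "For those found to be in need of treatment, medications are made available by a nurse".
- **Allocation and blinding.** Treating physicians and staff are told the allocation. The research nurses who collect outcome data are not.
- **Table 1.** Eligibility is assessed at both screening visits and again at the physician visit where treatment starts or referral is made.

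**The concern.** In a randomised comparison of time to an event, time zero should be a point that allocation cannot influence and that every randomised participant has. Randomisation is the natural choice. The stated origin is a clinical finding. On one reading of the protocol, that finding is made after allocation by clinicians who know the arm.

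Two things would then be at stake. First, time between randomisation and the finding of need would drop out of the outcome. If one arm takes longer to reach that finding, its delay is hidden. Second, a participant who is randomised but never judged in need has no start date and so cannot enter the analysis. Masking the research nurses does not help, because they do not make the clinical finding that starts the clock.

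**Working it through.** **Plan's own figures.** The only sample size given concerns sustained virologic response, not this outcome. It reproduces with the continuity-corrected two-proportion formula and n/(1 − 0.33):

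- 50% v 80%, 90% power: 58 per arm; 58/0.67 = 86.6, so 87, as stated.
- 50% v 75%, 80% power: 66 per arm; 66/0.67 = 98.5, so 99, as stated.

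Neither figure depends on the time origin, so none changes.

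**Where the origin falls.**

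| Section | What it implies |
|---|---|
| Eligibility criteria | Guideline eligibility is needed to enter the randomised trial: before allocation |
| Recruitment | Diagnosis of chronic HCV comes first, then randomisation: before allocation |
| Interventions, standard arm | Randomised participants are then assessed, diagnosed and found to need treatment: after allocation |
| Interventions, integrated arm | Need is established among those already randomised: after allocation |
| Table 1 | Eligibility assessed at both screenings and again at the initiation or referral visit: both |

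These statements cannot all describe one sequence, and Outcomes does not say which applies.

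**What follows if the origin comes after allocation.** Write total time T = L + P, where L is the lag from randomisation to the finding of need and P is the time from there to first dose. The stated outcome measures P only. With exponential P, the hazard ratio for P (integrated v standard) is mean P standard / mean P integrated, whatever L is.

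Take assumed means of P = 16 weeks standard and 12 weeks integrated, and L = 2 and 6 weeks. Mean T is 16 + 2 = 18 weeks and 12 + 6 = 18 weeks, so the arms do not differ in mean T. The hazard ratio for P is 16/12 = 1.33.

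Simulation with 100 per arm, exponential L and P, censoring at 52 weeks and 300 runs per row. Hazard ratios above 1 mean faster initiation in the integrated arm. Brackets give the share of runs with p < 0.05.

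| Mean L, std / int (weeks) | Mean P, std / int (weeks) | HR from randomisation | HR from finding of need |
|---|---|---|---|
| 2 / 6 | 16 / 12 | 0.99 (5%) | 1.33 (49%) |
| 6 / 2 | 12 / 16 | 1.01 (5%) | 0.76 (47%) |
| 4 / 4 | 16 / 16 | 1.00 (5%) | 1.00 (4%) |
| 12 / 12 | 16 / 16 | 1.00 (4%) | 1.00 (7%) |
| 4 / 4 | 16 / 12 | 1.32 (50%) | 1.33 (52%) |
| 8 / 8 | 16 / 12 | 1.32 (45%) | 1.37 (58%) |
| 26 / 26 | 16 / 12 | 1.17 (15%) | 1.34 (52%) |

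A repeat of the first row gave 1.02 (6%) and 1.36 (56%), so the percentages carry several points of simulation error.

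Unequal lags create an apparent benefit (row 1) or harm (row 2). Equal lags with no true difference create nothing (rows 3 and 4). A long equal wait counted inside the clock dilutes a real effect (last row).

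**The case against.** The strongest reply is that guideline eligibility is an inclusion criterion and that Recruitment randomises people already diagnosed. Read together, being in need of treatment under national guidelines is the state a participant must be in to be randomised. The origin then lies at or before allocation and cannot depend on arm. In addition, both arms are assessed at the same clinics, and Table 1 shows a single shared column for the initiation or referral visit, so nothing in the document points to unequal lags.

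Much of this stands. A reader might infer that the clock does start after allocation. The protocol does not establish that; it supports both orders. Nor does it show that the lags differ, so bias is possible but not demonstrated. What the reply does not remove is the wording of Interventions, which places diagnosis and the finding of need after randomisation in one arm and the finding of need after it in the other.

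A reader might also infer that the wait imposed by the earlier guideline is mixed into the outcome. That depends on the reading. Taken literally, an origin tied to need under national guidelines falls after the wait. The wait is counted only if the origin is the HCV diagnosis itself. Even then it would arise in both arms and, if balanced as the Discussion expects, would dilute rather than bias. The Discussion also expects most participants to be treated after the guideline change.

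Finally, it may be said that such detail belongs in the analysis plan still to be written. But the article states an origin, so the point is to correct a stated rule, not to supply a missing one.

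**Conclusion.** The point holds as a badly fixed time origin for a primary outcome. The stated origin is not randomisation, and the protocol places it on both sides of allocation. On the post-allocation reading it would be set by staff who know the arm. If the lag from randomisation then differs by arm, the Cox comparison can mislead in either direction, and participants never found in need would have no time zero.

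The size cannot be derived from the document, which gives only some weeks for the hospital appointment and some months for the guideline wait. The hazard ratios of 1.33 and 0.76, where the result from randomisation is close to 1, rest wholly on assumed exponential times and on a four-week difference in mean lag. They show direction and mechanism, not an expected bias in this trial. To say that the comparison has lost the protection of randomisation would go beyond the text.

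**What to change.** 1. In Outcomes, define time zero as the date of randomisation for every randomised participant.
2. Keep all randomised participants in the risk set until first dose or end of follow-up.
3. Reconcile Eligibility criteria, Interventions, Outcomes and Recruitment so that guideline eligibility is confirmed before allocation, and say what the eligibility assessment at the initiation or referral visit in Table 1 is for.
4. Report time from diagnosis to treatment start descriptively. The planned split into patient-related and system-related delay can stay.
5. If anyone was randomised before becoming guideline-eligible, add a sensitivity analysis starting at the later of randomisation and that person's own eligibility date. Set that date by the same objective rule in both arms: genotype, elastography result, or the guideline change of 1 February 2018. A common start at 1 February 2018 for all such people would not do. Someone with genotype 2 or 3 could become eligible earlier through an elastography result above 7.0 kPa, and could then start treatment before their own time zero.

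The cost is a change of wording and the use of a date that the electronic randomisation should already hold. There is a small downside: in the main analysis, any guideline wait after randomisation is counted in both arms and may dilute the hazard ratio. The sensitivity analysis in item 5 shows how much.
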